### Secondary Outcomes Analysis

We will perform analysis of covariance on the change of HbA_1c_ from the time consent is obtained to the end of the intervention period (at 12 weeks) or the end of the observation period (at 24 weeks), using the measurements at the time consent is obtained as covariates. The estimated mean change in each group and its 2-sided 95% CI will be calculated. Additionally, the estimated difference between groups and its 2-sided 95% CI will be calculated. The proportion of HbA_1c_ less than 7% at week 12 (E3) and week 24 (E4; or point of discontinuation, if earlier) will be compared between groups by the Fisher exact test.

The change from baseline in the clinical laboratory test values stated below at week 12 (E3) and week 24 (E4) (or point of discontinuation, if earlier) will be analyzed as the secondary outcomes:

 Weight (kg) BMI (kg/m^2^) Systolic and diastolic blood pressure (mmHg) Estimated glomerular filtration rate (ml/min/1.73 m^2^) Fasting blood glucose (mg/dL) Low-density lipoproteincholesterol (LDL-C; mg/dL) High-density lipoproteincholesterol (HDL-C; mg/dL) Triglyceride (mg/dL)

The percentages of participants at each stage of the transtheoretical model (TTM) stage of change will be calculated for both groups at the end of the intervention period (week 12) and the end of the observation period (week 24) were compared between groups using the Cochran-Mantel-Haenszel test.

Between-group changes in all TPB survey elements for dietary fiber, salt, and saturated fat intake (attitude, subjective norms, PBC, and intention) will be analyzed from the time of run-in to the end of 10 weeks, and to the end of the observation period (24 weeks), using repeated measures ANOVA with time (Week 1, Week 10, and Week 24) as a within-subjects factor and group (control vs intervention) as a between-subjects factor.

Changes in diabetes medications since consent acquisition at the end of the intervention period (at 12 weeks) and at the end of the observation period (at 24 weeks; classified as intensified, unchanged, and weakened) will be calculated for each group and compared between groups using the Cochran-Mantel-Haenszel test. The proportion of new medications added will be compared between groups by the Fisher exact test.

We will also calculate the percentage of responses for each option on the Likert scale and for the “Yes or No” scale in “Survey on participants’ satisfaction and perceived usefulness of the intervention” at the end of the intervention period for both intervention group and control group. For the “Survey on intention to improve eating habits using a Generative AI-enabled app”, we will calculate the percentage of responses for each option on the Likert scale at the end of the observation period for the intervention group.

As part of our exploratory analysis, we will assess the reliability of the TPB questionnaire using the Cronbach α coefficient. Additionally, we will conduct multivariate regression analyses to examine various associations related to the TPB constructs. Specifically, we will investigate the relationship between changes in intention (INT) to increase fiber intake and changes in fiber intake outcomes both between and within groups. Furthermore, we will analyze the associations between changes in attitude (ATT), subjective norms (SN), and PBC with changes in intention to increase fiber intake, as well as the relationship between changes in PBC and changes in fiber intake outcomes at both the between-group and within-group levels. The impact of the intervention on INT via ATT, SN, and PBC will be evaluated through mediation analysis.

We will calculate the frequency and weekly percentages of the following measurements during the intervention period in the intervention: number and percentage of days fiber goal is met out of 7 days, the number and percentage of implemented solutions in a week, the average weekly fiber change in the intervention group from run-in, and the average weekly energy change in the intervention group from run-in. We will also evaluate the effects of changes in dietary fiber intake on changes in BMI and HbA_1c_ using the Pearson correlation test and simple regression analysis.

We will perform a statistical analysis of safety outcomes by calculating the number and percentage of individuals who experience adverse events during run-in, intervention, and observation periods. During the intervention and observation periods, data will be compiled separately for the intervention and control group, and the percentages will be compared between groups using the Fisher exact test.

We will not apply statistical adjustment for multiple comparisons in the analysis of secondary and exploratory outcomes. We will interpret these results as exploratory and use them to inform future hypotheses.

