#### Official Study Enrollment and Randomization

Randomization will be conducted using a dynamic allocation method based on minimization, with an allocation ratio of 1:1. The allocation adjustment factors will include the baseline dietary fiber intake during run-in (under 10 g, 10 g and above), sex (male and female), and HbA_1c_ level on the date of consent (less than 8.5% and 8.5% or higher). Random allocation will be performed online using the INDICE cloud system provided by the University Hospital Medical Information Network (UMIN). After randomization, a CRC will explain the details of the intervention according to the study participants’ allocated group (intervention or control). Participants are blind to their group.

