### Sample Size Consideration

The primary outcome is the difference between the intervention group and the control group in the change in mean daily dietary fiber intake from the time of study enrollment to the end of the intervention period. We desired to detect a between-group difference in the mean change of 7 g of dietary fiber, drawing from a meta-analysis, which demonstrated a 9% risk reduction of cardiovascular disease events for 7 g increase in daily dietary fiber intake [47]. A previous RCT reported a 7.9 g/day increase in fiber intake at 3 months in the high-fiber group, supporting the use of a 7 g/day between-group difference as a realistic and meaningful target [33].

Based on the findings from a previous nutritional intervention research in Japan [48], we assumed a common SD of 9.85 g for the difference in dietary fiber change across both groups. Using a 2-sided significance level of 5% and a power of 80%, the required sample size calculated based on an independent *t* test is 33 participants per group. A study conducted in a similar population, which followed a similar study structure with a 2-week run-in phase, a 12-week intervention phase, and a subsequent 12-week observation phase by our research team showed minimal to no dropout throughout the study duration [49]. Nevertheless, as a conservative estimate to account for potential attrition, we aimed to enroll a minimum of 70 participants. The 2-week run-in phase also ensures that we enroll the participants who are able to use the app as instructed, thus minimizing drop-out risk.

Based on the findings from previous studies implemented in our research lab, we estimate a 10% dropout rate between preliminary and official study enrollment. Therefore, the target recruitment number for the preliminary study enrollment has been set at 77 participants.

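### HbA1c below 7% is compared by an unadjusted Fisher exact test: valid, but conservative at about 36 per arm and blind to baseline HbA1c, at a cost of roughly 4 to 18 points of power under assumed inputs

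*Protocol article*

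**What the plan says.** Under Secondary Outcomes Analysis, the proportion with HbA1c below 7% at week 12 and week 24, or "point of discontinuation, if earlier) will be compared between groups by the Fisher exact test". No covariate or stratum is named.

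Three other statements bear on this:

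- In the same section, change in HbA1c is analysed by analysis of covariance "using the measurements at the time consent is obtained as covariates", with the group difference and its 95% CI.
- Under Official Study Enrollment and Randomization, one of the three minimization factors is "HbA_1c_ level on the date of consent (less than 8.5% and 8.5% or higher".
- The section closes by declining multiplicity adjustment for secondary and exploratory outcomes: "We will interpret these results as exploratory and use them to inform future hypotheses".

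Textbox 1 requires HbA1c of at least 7.5% at consent, so nobody starts as a responder. Results reports 72 randomized, about 36 per arm. The article gives no responder rate, HbA1c SD or power for this outcome.

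**The concern.** The outcome is defined by a fixed threshold, and everyone starts at least half a point above it. A participant who enters at 7.6% is much likelier to cross 7% than one who enters at 9.5%, so baseline HbA1c should predict response. The plan uses it for allocation and for the mean-change model, but not here.

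Fisher's test is also conservative in samples of this size, because few tables have a p-value just under 0.05. At stake is sensitivity: a real difference in the proportion at target is more likely to be missed than it need be, although the data for a sharper analysis are already collected.

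**Working it through.** **The plan's own figure.** The only sample size in the article is for fiber intake: "We desired to detect a between-group difference in the mean change of 7 g of dietary fiber", and "we assumed a common SD of 9.85 g for the difference in dietary fiber change across both groups", with two-sided 5% and 80% power. The normal approximation is n = 2(1.960 + 0.842)² × (9.85/7)² = 2 × 7.85 × 1.980 = 31.1, so 32. With the noncentral t, power is 0.799 at 32 and 0.811 at 33. The stated 33 per group is reproduced. It says nothing about HbA1c below 7%.

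**True size of Fisher's test at 36 per arm.** For a common responder rate p,

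size(p) = Σₐ Σᵦ Bin(a; 36, p) × Bin(b; 36, p) × 1{Fisher two-sided p-value for (a, b) ≤ 0.05}.

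Full enumeration, with the mid-P version for comparison:

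| Common rate | Fisher | Mid-P |
|---|---|---|
| 5% | 0.3% | 1.2% |
| 10% | 1.4% | 3.4% |
| 15% | 2.3% | 4.6% |
| 20% | 2.6% | 4.8% |
| 30% | 2.8% | 4.5% |
| 50% | 2.5% | 4.4% |

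Fisher's maximum over all rates is 2.8% at 36 per arm (2.9% at 35, 3.6% at 33).

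**Power lost to conservatism alone** (exact, 36 per arm, assumed rates). Fisher against mid-P: 0.345 v 0.471 at 5% v 20%; 0.472 v 0.575 at 10% v 30%; 0.405 v 0.498 at 15% v 35%; 0.696 v 0.756 at 20% v 50%. The loss is about 6 to 13 points.

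**Adding baseline HbA1c** (simulation, 4000 trials per setting, 36 per arm; every input is an assumption). Baseline is 7.5 plus a gamma variable, mean about 8.4. Follow-up is 8.4 − m + 0.7 × (baseline − 8.4) − effect + normal error, with m = 0.3, 0.6 or 0.9, effect 0.3 or 0.5 points, and residual SD 0.6 or 1.0. The baseline/follow-up correlation is about 0.44 to 0.63. The adjusted test is logistic regression on baseline HbA1c, recalibrated to a true 5% size.

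| Residual SD | Rates, control v intervention | Fisher | Mid-P | Adjusted | Adjusted − Fisher |
|---|---|---|---|---|---|
| 0.6 | 6% v 13% | 7.4% | 13.2% | 16.5% | 9.1 |
| 0.6 | 6% v 20% | 31.6% | 44.4% | 44.1% | 12.5 |
| 0.6 | 13% v 24% | 15.9% | 22.8% | 24.6% | 8.7 |
| 0.6 | 13% v 34% | 46.6% | 56.0% | 60.7% | 14.1 |
| 0.6 | 24% v 39% | 20.1% | 25.6% | 31.0% | 10.9 |
| 0.6 | 24% v 50% | 51.7% | 59.2% | 70.0% | 18.3 |
| 1.0 | 15% v 22% | 7.3% | 11.5% | 12.1% | 4.8 |
| 1.0 | 15% v 28% | 19.2% | 27.2% | 28.6% | 9.4 |
| 1.0 | 23% v 32% | 9.1% | 12.8% | 13.5% | 4.4 |
| 1.0 | 23% v 38% | 21.9% | 28.3% | 31.5% | 9.6 |
| 1.0 | 32% v 42% | 9.1% | 12.6% | 14.9% | 5.8 |
| 1.0 | 32% v 49% | 23.6% | 30.1% | 34.2% | 10.6 |

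The total gap is 4.4 to 18.3 points. In 11 of the 12 rows the step from Fisher to mid-P is the larger part; the exception is 24% v 50% (7.5 points from mid-P, 10.8 from baseline).

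**The candidate replacements.** In separate simulations under three sets of assumptions, a 0.5-point effect gave power of 21–42% with Fisher, 29–55% with an unstratified chi-square, 30–56% with Cochran-Mantel-Haenszel stratified at 8.5%, and 32–59% with a baseline-adjusted logistic score test. The stratified and score tests ran at about 4.6 to 5.9% size. The uncalibrated logistic likelihood-ratio test ran at 5.6 to 8.6% in the settings tabulated above, worst with fewest responders.

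**The case against.** The strongest reply is that nothing here is wrong. Fisher's test holds its error rate however few respond, which is a fair reason to choose it for a possibly sparse outcome. That stands.

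Second, Objective 2 concerns HbA1c levels, and the baseline-adjusted analysis of covariance answers it. At residual SD 0.6 (assumed) that analysis has power of about 0.55 for a 0.3-point effect and 0.93 for 0.5. Cutting HbA1c at 7% loses much more than the choice of test, and the fix keeps the cut. This also stands. A reader might infer that the trial discards a large share of its power on HbA1c; the documents do not support that, because the loss falls on one supplementary outcome among many that are labelled exploratory.

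Third, stratifying at 8.5% adds little beyond an ordinary chi-square. That is right, and the gain should not be credited mainly to baseline. A reader might also infer that ignoring a minimization factor inflates the error rate. The effect is the reverse: with allocation balanced within the 8.5% strata, Fisher's size in one simulated setting fell to 1.8–2.0%.

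What does not stand is that the choice belongs to an unseen analysis plan. The article names the test, and a more sensitive one needs no new data.

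**Conclusion.** The point holds as an efficiency improvement to one exploratory secondary outcome. The conservatism follows from the design alone: at 36 per arm Fisher's size never exceeds 2.8%, whatever the common responder rate. A single figure of about 2% would be too firm, since the size falls to 0.3% at a 5% rate and the article states no rate.

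The power loss of roughly 4 to 18 points depends on assumed rates, SDs, effects and baseline correlation, so it should be quoted only as a range. Most of it is Fisher's conservatism; baseline adjustment usually adds a few points. It is not an error or a contradiction, and neither the primary analysis nor the HbA1c analysis of covariance is touched.

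**What to change.** Before anyone sees outcome data by arm, change the main comparison of HbA1c below 7% at weeks 12 and 24 to one of these:

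- a Cochran-Mantel-Haenszel test stratified by the minimization category (below 8.5% v 8.5% or higher), a method the same section already uses for other outcomes; or
- logistic regression with baseline HbA1c as a continuous covariate, tested by the score statistic or fitted with Firth's penalty. Avoid the plain likelihood-ratio test.

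Report the adjusted risk difference with its 95% CI, and keep Fisher as a sensitivity check.

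The cost is a few lines of wording and no new data. The downside is that asymptotic tests are unreliable with very few responders. Prespecify a mid-P, exact or penalized fallback and the responder count that triggers it, and accept that some of the power gain is then lost.

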#### Study Events

This study includes 5 events (E0-E4), a 2-week run-in period, a 12-week intervention period, and a 12-week observation period. Study participant experience and data collected in different stages of the study are described in Table 3.

**Table 3. T3:** Study events spanning approximately 26 weeks.

Event	Time	Key activities	
E0	Preliminary study enrollment	Participant experience: obtain consent to participate in study. Data collected: Patient background^a^, vital signs^b^, hematological tests^c^, biochemical tests^d^, urinalysis^e^, medication status survey, and the transtheoretical model (TTM) questionnaire for dietary behavior change^f^.	
Run-in period	From E0 for 2 weeks	Participant experience: Log meals with MealLog app Data collected: Number of days with at least 2 logged eating occasions (main meals or snacks), total fiber intake per day (grams), average fiber intake (excluding days with only 0 or 1 logged meal), theory of planned behavior (TPB) questionnaire for dietary fiber intake^g^, TPB questionnaire for salt intake^g^, and TPB questionnaire for saturated fat intake^g^.	
E1	At the time of official study enrollment	Intervention group: Participant experience: Download FiberMore and receive educational handout on dietary fiber intake. Data collected: Medication status and system defects.	
		Control group: Participant experience: Receive educational handout on salt reduction. Data collected: Medication status and system defects.	
Intervention period	From E1 for 12 weeks	Intervention group: Participant experience: Interact with FiberMore. Data collected: The number and percentage of days fiber goal is met out of 7 days, the number and percentage of implemented coping strategies per week, the average estimate of fiber intake per day (excluding days with only 0 or 1 logged meal), and the average estimate of energy intake per day (excluding days with only 0 or 1 logged meal).	
		Control group: Participant experience: Record salt reduction efforts in a paper diary (sham intervention), receive 1-time educational weblink on salt reduction via an SMS text message during week 4 and week 8, and use MealLog to log meals during week 11 and week 12. Data collected: During week 11 and week 12—the average estimate of fiber intake per day (excluding days with only 0 or 1 logged meal) and the average estimate of energy intake per day (excluding days with only 0 or 1 logged meal).	

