d Biochemical tests (performed at least a week before each time point): estimate glomerular filtration rate (eGFR), creatinine, fasting blood glucose, HbA_1c_, low-density lipoprotein cholesterol (LDL-C), high-density lipoprotein cholesterol (HDL-C), triglycerides, albumin, blood urea nitrogen (BUN), and potassium.

e Urinalysis (performed at least a week before each time point): Urine protein and urine-albumin-creatine ratio (UACR).

f Transtheoretical model (TTM) questionnaire: Measure the 5 stages of dietary behavior change in TTM: Precontemplation, contemplation, preparation, action, and maintenance. Amount of dietary fiber intake: artificial intelligence (AI) assessment of dietary fiber intake via meals logged onto the app.

g The theory of planned behavior (TPB) questionnaire: Measure attitude, subjective norms, perceived behavioral control, and intention to improve dietary behavior.

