#### Secondary Outcomes

Secondary outcomes (see Table 4) include clinical and health measures, measurements of behavior changes, engagement measures with intervention features, and assessments of participants’ satisfaction and perceived usefulness of the intervention. We will also assess the occurrence of adverse events via patient interviews.

**Table 4. T4:** Secondary outcome measures.

Measurements	Outcomes
Difference in changes	HbA_1c_ (%)^a^ Weight (kg)^a^ BMI (kg/m^2^)^a^ Systolic and diastolic blood pressure (mmHg)^a^ Estimate glomerular filtration rate (eGFR; ml/min/1.73m2)^a^ Fasting blood glucose (mg/dL)^a^ Low-density lipoprotein cholesterol (LDL-C; mg/dL)^a^ High-density lipoprotein cholesterol (HDL-C; mg/dL)^a^ Triglyceride (mg/dL)^a^ Theory of planned behavior (TPB) elements for dietary fiber, salt, and saturated fat intake (attitude, subjective norm, perceived behavioral control, and intention).^b^
Difference in proportions	Transtheoretical model (TTM) stage of change questionnaire for dietary behavior.^a^ Changes in antidiabetic drugs since consent was obtained (intensified, unchanged, and weakened).^a^ Usage of each antidiabetic drug.^c^
Measured values	Average estimate of fiber intake per day.^d^ Average estimate of energy intake per day.^d^ Number and percentage of days fiber goal is met out of 7 days.^d^ Number and percentage of implemented solutions in a week.^d^ Survey on participants’ satisfaction and perceived usefulness of the intervention.^e^ Percentage of patients with HbA_1c_ less than 7%.^f^ Survey on intention to improve eating habits using a generative artificial intelligence (AI)-enabled app^g^

a Difference in change from the time consent was obtained to the end of the intervention period (12 weeks) and to the end of the observation period (24 weeks).

b Difference in change from the time of run-in to the end of 10 weeks and to the end of the observation period (24 weeks).

c Calculated at the time of consent acquisition, at the time of official study enrollment, after the end of the intervention period, and after the end of the observation period.

d Evaluated weekly from week 1 to 12 for the intervention group.

e Percentages of responses for each option on the Likert scale and for the Yes or No scale will be calculated after the end of the intervention period for the intervention group and control group.

f Evaluated at the end of week 12 and week 24 for both intervention group and control group.

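### The stage-of-change outcome is defined as a change from consent, but the described Cochran-Mantel-Haenszel comparison uses only the follow-up stages and gives the consent stage no part

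*Protocol article*

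**What the plan says.** **Definition.** Secondary Outcomes, Table 4, lists the TTM stage among the outcomes measured as differences in proportions and attaches footnote a: "Transtheoretical model (TTM) stage of change questionnaire for dietary behavior.^a". The footnote reads "Difference in change from the time consent was obtained to the end of the intervention period (12 weeks", and continues to the end of the observation period at 24 weeks.

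**Analysis.** Secondary Outcomes Analysis says "The percentages of participants at each stage of the transtheoretical model (TTM) stage of change will be calculated for both groups" at weeks 12 and 24, and that these "were compared between groups using the Cochran-Mantel-Haenszel test". It names no stratification variable, CMH statistic or stage scores.

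**Measurement.** Study Events, Table 3, lists among the data taken at E0 the "medication status survey, and the transtheoretical model (TTM) questionnaire for dietary behavior change". A note to that table gives the scale: "Measure the 5 stages of dietary behavior change in TTM: Precontemplation, contemplation, preparation, action, and maintenance". Textbox 1 admits participants in three of these five stages: contemplation, preparation and action.

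**Allocation.** Official Study Enrollment and Randomization says "The allocation adjustment factors will include the baseline dietary fiber intake during run-in", then adds sex and HbA1c. TTM stage is not among the factors.

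**The concern.** A change from consent and a stage distribution at follow-up are different quantities. Someone who enters in action and stays there is counted at week 12 exactly like someone who moved up from contemplation. Only the second has changed in the sense of footnote a.

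The neighbouring analyses do use the starting point. HbA1c is analysed by ANCOVA with the consent value as covariate. The theory of planned behavior scales enter a repeated-measures model with an early time point. The drug outcome is itself coded as change since consent. TTM stage carries the same footnote as HbA1c and drug change, but its described analysis has no baseline element.

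Two things are at stake. The reported result would not be the outcome that Table 4 names. Differences in starting stage would also stay in the error term, with no described correction for chance imbalance between small arms.

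**Working it through.** **1. The plan's own figures.** The plan gives no power figure for the TTM outcome. Its only sample size is for fiber intake: difference 7 g, SD 9.85 g, two-sided 5%, power 80%. The t-test solution is 32.07 per group, rounded up to the stated 33 (power 81.1%), so that figure reproduces. Per-arm numbers for the TTM check are 70/2 = 35 (minimum enrolment) and 72/2 = 36 (randomized as of September 22, 2025).

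**2. What a CMH test does with and without a stratum.** In the mean-score form, with integer stage scores, stratum *h* contributes:

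- U_h = (sum of scores in the intervention arm) − n_1h × (mean score in the stratum)
- V_h = n_1h n_0h / [n_h (n_h − 1)] × Σ(score − stratum mean)²
- Q = (Σ U_h)² / Σ V_h, on 1 df

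With no stratum there is one term, and all spread in starting stage stays in V. With strata formed by consent stage, only the spread within a starting stage remains. Within such a stratum, change equals follow-up score minus a constant. U_h and V_h are therefore the same whether one scores follow-up or change, so the stratified test addresses footnote a directly.

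The general-association form treats the stages as unordered. Without a stratum it equals Pearson's chi-square × (N − 1)/N. A check with N = 70 gave 3.279 on 4 df, p = 0.512, by both routes.

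**3. Size.** The documents give no consent distribution, follow-up distribution or correlation, so all three are assumed. Stages are cut from a bivariate normal variable, consent stage falls in equal thirds, and each setting has 2000 runs.

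- 0.5-SD shift: 36 per arm; follow-up cut at control-arm cumulative proportions of 8, 33, 62 and 90%.
- 0.6-SD shift: 35 per arm; follow-up cut at −1.3, −0.4, 0.4 and 1.3.

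Power of the mean-score CMH test:

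| Shift | Correlation | No stratum | Stratified by consent stage | Gain (points) |
|---|---|---|---|---|
| 0.5 SD | 0.3 | about 51% | 52% | about 1 |
| 0.5 SD | 0.5 | about 52% | 58% | about 6 |
| 0.5 SD | 0.7 | about 52% | 71% | about 19 |
| 0.6 SD | 0.3 | 63.45% | 65.55% | 2.1 |
| 0.6 SD | 0.5 | 65.55% | 73.70% | 8.15 |
| 0.6 SD | 0.7 | 65.60% | 83.65% | 18.05 |

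The unstratified 0.5-SD entries are the stratified power minus the gain. The Monte Carlo standard error of one entry is about √(0.65 × 0.35/2000) = 1.1 points, so the gain at correlation 0.3 is close to nil.

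With no shift, rejection rates were about 4 to 6% for the tests compared.

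**4. If the unordered form were used.** Unstratified general association has power 29, 25 and 27% at 0.5 SD (correlation 0.3, 0.5, 0.7). Against the stratified mean-score test that is 52 − 29 = 23, 58 − 25 = 33 and 71 − 27 = 44 points lower. At 0.6 SD it has 37.7, 40.0 and 40.8%, which is 27.9, 33.7 and 42.9 points lower.

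**The case against.** **The strata and the CMH statistic may be in an unseen plan.** This stands. An article commonly leaves such detail out, so its absence alone is no finding. What does not depend on the unseen plan is that two statements in the article describe different quantities.

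**Footnote a is shared by many outcomes and may only give the time horizons; the row heading fits a comparison of percentages.** This narrows the conflict to the footnote against the analysis text. The footnote still says change from consent, and the TTM analysis describes none.

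**No TTM hypothesis is stated.** This is correct. The listed objectives concern fiber intake and HbA1c. Secondary outcomes are not adjusted for multiplicity and are to be read as exploratory. That limits the weight of the point.

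**Stronger readings.** A reader might infer that the plan ignores the order of the stages and so loses 23 points or more. The article does not say so: CMH includes ordered statistics. The article uses Fisher's test for its between-group comparisons of binary outcomes and CMH only for two outcomes with ordered categories, which is at least compatible with an ordered form. A reader might also extend the point to drug changes, but that outcome is already coded as change since consent, in agreement with Table 4.

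**Conclusion.** The mismatch holds. Footnote a defines a change from consent, and the described analysis compares stages at follow-up without the consent stage. The randomized comparison remains valid with its nominal error rate. It answers a somewhat different question from the one defined, and probably less efficiently.

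If ordered scores are already intended, the power forgone is about 1 to 19 points, depending mainly on how strongly the consent stage predicts the later stage. This range rests on latent-normal stages, equal thirds at consent and assumed correlations. It would be smaller if most participants entered in one stage, and zero if the unseen plan already stratifies by consent stage. It would be larger only if the unordered form were used. Even the stratified test has only 52 to 71% power at 0.5 SD, so much of the risk of missing a shift comes from the sample size.

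Severity: consider. The primary and HbA1c analyses are not affected.

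**What to change.** In Secondary Outcomes Analysis, state that TTM stage at week 12 and at week 24 will be compared between groups with the CMH row-mean-score test, using integer stage scores and stratified by TTM stage at consent (contemplation, preparation, action). This brings the analysis into line with footnote a.

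Rewording footnote a for this outcome, as the stage distribution at weeks 12 and 24, would also remove the contradiction. It would leave the collected baseline unused.

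The cost is a change of wording. All the data are already scheduled. The small downside is that integer scores treat the stages as equally spaced. The choice should be fixed before the group comparison is run, so that the form of the test cannot depend on the results.
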